Objectives 1c, 1d, 4 and 5 are conditional to sufficient resources still being found to conduct the laboratory analyses required, and will not be further discussed in this plan.

1. **Study type and key design features**

The study concerns an individually-randomised, controlled non-inferiority trial with three parallel arms, with participants randomised to daily home fortification for 30 days with sachets containing either a) 3 mg iron as NaFeEDTA (experimental treatment); b) 12.5 mg iron as encapsulated ferrous fumarate (positive control); or c) placebo (negative control).

Demonstration of non-inferiority in a trial with two arms can have two meanings only: both interventions are equally effective, or both interventions are equally ineffective against placebo. Thus, as per guidelines of the European Medicine Agency [1] and the International Conference on Harmonisation of Technical Requirements for Registration of Pharmaceuticals for Human Use [2], we included a third arm with placebo, which allows a) demonstration of superiority of home fortification with 3mg iron as NaFeEDTA over placebo (proof of efficacy); b) demonstration of superiority of the reference (12.5 mg iron as encapsulated ferrous fumarate) over placebo (proof of assay sensitivity); and c) demonstration that the home fortification with 3mg iron as NaFeEDTA retains most of the efficacy of the reference over placebo (proof of non-inferiority).

Haemoglobin concentration at baseline was strongly expected to be prognostic for haemoglobin concentration at the end of intervention. To achieve group balance in size and baseline haemoglobin concentration, randomisation was based on a stratified block design, with strata defined by baseline haemoglobin concentration class (<100 g/L and ≥100 g/L) and randomly sized permuted blocks of 6 or 9. Stratification at the stage of randomisation and adjustment for this stratification in the analysis was also expected to improve the efficiency of the analysis and the precision of the estimated intervention effect. Because of the short recruitment period, we did not expect blocks to be associated with haemoglobin concentration, even though we could not entirely exclude this possibility (e.g. due to seasonal changes in diet or malaria transmission). We did not conduct interim analyses and had no stopping guidelines.

**Figure S1:** **Summary of study design (not to scale)**.

1. **Sample size calculations**

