The target sample size was 108 participants per group, which was determined using procedures and terminology for sample size calculations in non-inferiority trials as recommended by US Food and Drug Administration [3,4]

1. Based on a meta-analysis [5], we estimated the effect of 12.5 mg ferrous fumarate on haemoglobin concentration relative to placebo. The lower limit of the 95% CI thus obtained (9.3 g/L) was used as M_1_, the minimum anticipated effect of 12.5 mg ferrous fumarate in our trial (**Figure 2;** left panel).
2. Next, we set M_2_ as the margin specified to preserve 50% of the anticipated minimum effect of 12.5 mg ferrous fumarate anticipated reduction in the 3mg NafeEDTA test treatment. This margin (haemoglobin concentration of 4.7 g/L) can be interpreted as the largest loss of effect compared to 12.5 mg ferrous fumarate (inferiority) that would be acceptable, and also is below an effect for 5g/L haemoglobin concentration that we consider to be of minimum importance for public health.
3. We set the sample size so that the lower limit of the 95% CI around the difference in haemoglobin concentration between the two iron formulations (i.e. 12.5 mg ferrous fumarate and 3.0 mg iron as NaFeEDTA) would lie above M2 (Figure 1; right panel).

Peer reviewers or editors of scientific journals may demand that we report sample size calculations and statistical power. Although such calculations are critically important in planning a study, we consider statistical power to be an exclusively pre-trial concept, which is irrelevant and conceptually wrong in the interpretation of study results, based on assumptions that are not usually met during trial implementation, and prone to be misinterpreted by most readers [6,7]. Thus we intend to refrain from reporting sample size calculations, but we will report the method used to determine the non-inferiority margin.

[figure not shown]

Figure S2: Theoretical framework for sample size determination

1. **Software**

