| Plasma vitamin B_12_ concentration | Continuous | pmol/L |

* Funds permitting

1. **General issues in the analysis of intervention effects**

Effects are measured by comparing outcomes measured after a particular intervention with those measured if an alternative intervention has been given (counterfactual argument), thus focusing on comparison of end points (instead of before-after measurements within groups). We will estimate effects when possible; P-values, where reported, will be 2-sided. We will avoid hypothesis testing and interpretation of results as ‘significant’ or p<0.05 for reasons reported elsewhere [14,15].

We will describe outcome variables by intervention groups as proportions, means (SD), geometric means (geometric SD), and median (25^th^- and 75^th^ percentiles) as appropriate, with corresponding group sizes. For continuous outcomes, these estimates will be obtained by ANOVA.

Intervention effects will be assessed as absolute differences (proportions and means) or relative differences in geometric means (variables with lognormal distributions) between groups, with accounting for the stratified block design. To facilitate interpretation, odds ratios resulting from these analyses will be converted to differences in proportions. To allow extrapolation of results to other settings, we will also consider reporting relative effects for binary outcomes (i.e. proportion ratios). Outcomes that are not normally distributed, even after log-transformation, will be compared using non-parametric tests (e.g. Mann-Whitney U test, or Wilcoxon rank sum statistics)

1. **Analysis of the primary outcome (objective 1a and 2)**

*Primary analysis:* We will estimate the difference in haemoglobin concentrations at the end of the 30-day fortification period between groups of children allocated to different iron formulations. Non-inferiority will be rejected if the difference between groups is less than the non-inferiority margin.

*Secondary analysis* of the primary outcome will be as follows:

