1. *Adjustment* *for selected baseline variables:* Biased effect estimates would occur if there are group imbalances in baseline factors that are prognostic for outcome. For baseline factors that are known to be strongly, or at least moderately, associated with the primary outcome, or for which there is a strong biological rationale for such an association, i.e. iron status, plasma soluble transferrin receptor concentration, and age, we will evaluate the role of such bias using stratified analysis and directly by multiple linear regression models. We also expect haemoglobin concentration at baseline to be prognostic for outcome but, because this will already be accounted for by adjusting for study design. In stratified analysis, we will estimate intervention effects in subgroups formed by these baseline factors (for iron status: see definition in Table 1; plasma soluble transferrin receptor concentration dichotomised with the median as cut-off value; and age in classes of children aged 12-23 months and 24-30 months) to allow an assessment of the validity of model assumptions. In the regression models, we will compare effect estimates with and without adjustment by baseline factors (plasma concentrations of ferritin and soluble transferrin receptor and age; as continuous variables). In the interpretation of data, we will give priority to the unadjusted effect, unless the adjusted effect is markedly different (>15%), in which case the adjusted effect will be considered the primary analysis.

*Subgroup analysis:* Because iron absorption is known to depend on iron status, we will consider proxy markers for iron status (haemoglobin concentration, plasma concentrations of ferritin and soluble transferrin) at baseline as potential modifiers for intervention effects.

Stratified analysis will be used to measure effect sizes within subgroups. Evidence for group differences in intervention effects will be formally investigated in a multiple regression model with main effects (for baseline factors and the intervention) and multiplicative interaction terms.

To define subgroups, baseline factors will be categorized (haemoglobin concentration class <100 g/L and ≥100 g/L; iron status [see classification above] and plasma soluble transferrin receptor concentration [dichotomised, with the median as threshold]). For iron status, we will restrict the analysis to a comparison of iron-deficient and iron-replete subgroups.

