Categorisation of baseline factors has the advantage that results can be conveniently presented in a forest plot. It has the disadvantage, however, that the precision of the interaction depends on the number and position of the cut-off values used to categorise baseline factors [16]. We will also explore interactions with baseline factors as continuous covariates, using fractional polynomials [16]. Such a strategy is more powerful, especially at towards extreme ends of the covariate distribution where limited numbers of observations generally preclude detection of interaction, and it may reveal more about the nature of possible interactions. We will inspect scattergrams and conduct sensitivity analysis as needed to examine the influence of possible outliers on results.

Results of subgroup analyses will be interpreted cautiously for reasons reported elsewhere [13].

1. *Intention-to-treat analysis:* For binary outcomes, pooled estimates from multiple iterations may result in non-integer values. This precludes computation of confidence intervals for differences in proportions, and may be counterintuitive to readers not well versed in multiple imputation techniques. To handle this problem, we will calculate differences in means under the assumption of binary outcome variables having a Bernoulli distribution. Pooled chi-squared statistics for cross-tabulated data and associated p-values will be calculated as described by Van Buuren (2012), thus the p-values obtained are only crude estimates of the true values [17].
2. *Paired comparisons of iron groups with placebo (objective 2):* This analysis will be done as for the comparison between iron groups (see above). Superiority will be established if no effect is excluded from the 95% CI.
3. **Analysis of secondary outcomes (objectives 1b and 2)**

To assess intervention effects, we will conduct all three possible paired comparisons between the intervention groups. We will use plasma ferritin concentration as an outcome indicator of iron status, and soluble transferrin receptor as an outcome indicator of the iron demand by the erythrocytes (both measured at the end of the 30-day intervention period). We will conduct analysis with and without adjustment for baseline factors, as well as intention-to-treat analysis (see methods above).

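### Adjusting for baseline haemoglobin only through the 100 g/L stratum gives up precision that the continuous value would provide at almost no cost

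*SAP*

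**What the plan says.** Under Study type and key design features, the SAP states: "Haemoglobin concentration at baseline was strongly expected to be prognostic for haemoglobin concentration at the end of intervention". Randomisation is stratified on this variable alone, with "strata defined by baseline haemoglobin concentration class (<100 g/L and ≥100 g/L"). The same section says that "adjustment for this stratification in the analysis was also expected to improve the efficiency of the analysis and the precision of the estimated intervention effect".

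Under General issues in the analysis of intervention effects, effects are to be estimated as differences "between groups, with accounting for the stratified block design". This is the only adjustment that applies to the primary estimate.

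Under Analysis of the primary outcome, the secondary analysis on adjustment for baseline variables enters "plasma concentrations of ferritin and soluble transferrin receptor and age; as continuous variables". Baseline haemoglobin is acknowledged as prognostic but is not listed, "because this will already be accounted for by adjusting for study design". That sentence is grammatically unfinished, though its sense is clear. The unadjusted effect keeps priority unless the adjusted one differs by more than 15%.

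Continuous baseline haemoglobin can enter only the subgroup work: "We will also explore interactions with baseline factors as continuous covariates, using fractional polynomials".

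**The concern.** The study design carries baseline haemoglobin as a yes/no split at 100 g/L, plus randomisation blocks that the SAP does not expect to be related to haemoglobin. Adjusting for that split removes the difference between the two classes. It removes nothing within a class, where children just above the cut are treated the same as children far above it. So the stated reason for omitting the continuous value does not hold.

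The SAP is also uneven here. Soluble transferrin receptor and age are grouped for the stratified analysis but entered as continuous variables in the regression. In its discussion of interactions the SAP notes that categorising makes precision depend on the cut-offs and that continuous covariates are more powerful. Of the factors it names as prognostic, only the outcome's own baseline value stays at two classes in the effect estimate.

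What is at stake is interval width. Non-inferiority is read from a 95% confidence interval against a 4.7 g/L margin, and it is accepted only if both placebo comparisons also succeed. The loss of precision therefore falls on all three contrasts.

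**Working it through.** **The plan's own figures.** Half of M1 is 0.5 × 9.3 = 4.65 g/L, which agrees with the stated 4.7. For the sample size, "The target sample size was 108 participants per group". This cannot be reproduced, because the SAP gives no SD, power or dropout. Solving n = 2 × [SD × (z₀.₉₇₅ + z_power) / 4.7]² backwards with n = 108, a true difference of zero and no dropout gives:

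- 80% power: SD = 4.7 × √54 / 2.802 = 12.3 g/L
- 90% power: SD = 4.7 × √54 / 3.242 = 10.7 g/L

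**Inputs for the check.** The cut at 100 g/L and the 108 per group come from the SAP. The SAP does not give the correlation r between baseline and end haemoglobin, or the share of children below 100 g/L. I assume r from 0.4 to 0.7, a share of 21% to 50%, a normal baseline distribution and a linear relation.

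**Step 1: what the split captures.** With the cut at c standard deviations from the mean, the share f of the baseline variance captured by the two classes is f = φ(c)² / [Φ(c)(1 − Φ(c))].

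- Cut at the median (50% below, c = 0): 0.3989² / 0.25 = 0.637. This is the maximum.
- 21% below (c = −0.8): 0.2897² / (0.2119 × 0.7881) = 0.503.

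So at least 36% of what the continuous value explains is left in the residual.

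**Step 2: effect on the interval.** Residual variance, as a share of outcome variance, is 1 − r²f with the stratum only and 1 − r² with the continuous value. The variance ratio is (1 − r²)/(1 − r²f), and its square root is the ratio of interval widths. For example, at r = 0.5 and f = 0.637: 0.75 / (1 − 0.25 × 0.637) = 0.892, and √0.892 = 0.944, which is a 6% narrowing. The equivalent group size is 108 divided by the variance ratio.

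| r | Variance ratio (50% / 21% below) | Width ratio | Narrowing | Equivalent n per group |
|---|---|---|---|---|
| 0.4 | 0.935 / 0.913 | 0.967 / 0.956 | 3–4% | 115–118 |
| 0.5 | 0.892 / 0.858 | 0.944 / 0.926 | 6–7% | 121–126 |
| 0.6 | 0.830 / 0.781 | 0.911 / 0.884 | 9–12% | 130–138 |
| 0.7 | 0.741 / 0.677 | 0.861 / 0.823 | 14–18% | 146–160 |

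**Step 3: scale against the margin.** Suppose 108 per group gives 80% power with stratum adjustment, so that the residual SD is 12.3 g/L. The half-width is then 1.96 × 12.3 × √(2/108) = 3.28 g/L. Continuous adjustment brings it to between 3.28 × 0.967 = 3.17 and 3.28 × 0.823 = 2.70 g/L. Power, Φ(2.802 / width ratio − 1.960), becomes about 83% at r = 0.4, 84–86% at 0.5, 87–89% at 0.6 and 90–93% at 0.7.

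**Step 4: simulation.** Two arms of 108 with stratified allocation, 4,000 runs per scenario and 20%, 30% or 50% below the cut gave standard-error ratios (continuous plus stratum against stratum alone) of 0.93–0.95 at r = 0.5, 0.88–0.91 at 0.6 and 0.81–0.85 at 0.7. These agree with the formula.

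**The case against.** The best defence is that stratifying on a prognostic factor and adjusting for the stratum is a recognised and valid approach. That stands. Nothing here shows bias, wrong coverage or inflated error. A wider interval makes non-inferiority and both superiority conditions harder to show, so the omission does not favour a false claim.

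It can also be said that the size is built on assumptions. That stands too. The SAP gives no correlation and no share below 100 g/L, so no part of the 3–18% range can be preferred from the document, and at r = 0.4 the gain is small.

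The sentence does sit in a paragraph about imbalance, and stratification does limit imbalance across the cut. Continuous ferritin, soluble transferrin receptor and age may recover some of the explained variance in the adjusted model. But that model becomes primary only under the 15% rule, and the fractional-polynomial work concerns interactions. Neither restores precision to the estimate that has priority.

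Two stronger readings are tempting, and the SAP does not support them:

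- **That baseline haemoglobin is the strongest predictor.** The SAP says it was strongly expected to be prognostic, which describes the expectation, not the strength of association. It does not rank haemoglobin against iron status, transferrin receptor or age.
- **That chance imbalance within strata is a further harm.** Under randomisation, such imbalance is already part of the sampling variance that the interval reflects. It is the same loss of precision seen from another side.

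**Conclusion.** The point holds as a free improvement. The reason given for omitting continuous baseline haemoglobin is wrong, because the 100 g/L split captures at most about 64% of the variance that the continuous value explains (under normality), and about 50% if 21% of children lie below the cut. The planned analysis remains valid but gives up precision on the non-inferiority contrast and both placebo contrasts.

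The narrowing available is about 3–18% of interval width, and where it falls in that range depends mainly on the correlation. This rests on assumed correlations of 0.4–0.7, an assumed 21–50% below 100 g/L, normality and linearity. It would be smaller with a weaker correlation. A reader should not infer that the trial's conclusions would be biased or that a non-inferiority claim would be unsafe for this reason.

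**What to change.** - In Analysis of the primary outcome, state that the primary model for every haemoglobin contrast (between iron formulations, and each iron group against placebo) includes the randomisation stratum and baseline haemoglobin as a continuous covariate, in both the per protocol and the intention-to-treat analysis.
- Replace the unfinished sentence that says adjustment for study design already accounts for baseline haemoglobin.
- State that this model supplies the reference estimate for the 15% comparison, so that further adjustment for ferritin, transferrin receptor and age is judged against it.

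The cost is SAP wording and about one degree of freedom in some 216 children per pairwise contrast (2 × 108). No new data are needed, since each child's stratum was assigned from this measurement. The SAP's own imputation rule, which includes all variables used in the regression models, then covers the covariate. The SAP says it was finalised before the randomisation code was broken, so the change could have been pre-specified. If made after that, the result should be labelled as supportive.

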### Additional file 1: Statistical analysis plan

[name], [name]

Version 19^th^ May 2015

1. **Preamble**

This plan was developed to analyse data from the SEICK (Safe and Effective Iron for Children in Kenya) trial. The study received ethical clearance in Kenya (Kenyatta University National Hospital/University of Nairobi, #KNH-ERC/A/402)) and in England (London School of Hygiene and Tropical Medicine, #6503)), and was registered at ClinicalTrials.gov (NCT02073149). The principal features of the planned analysis were established as part of the trial proposal. The current plan provides an update, was finalised after data collection but before breaking the randomization code, and should take precedence over the trial proposal.

1. **Trial objectives**

The study was primarily conceived to assess non-inferiority of daily home fortification with 3mg iron as NaFeEDTA compared with 12.5 mg iron as encapsulated ferrous fumarate, with haemoglobin concentration at the end of the 30-day intervention period as the primary outcome.

The study proposal states the following objectives:

1. In children aged 12-36 months, to compare daily home fortification for 30 days with two iron formulations (3mg iron as NaFeEDTA versus 12.5 mg iron as encapsulated ferrous fumarate) regarding:
2. Haemoglobin concentration at the end of the 30-day fortification period ***(primary objective)***;
3. Iron status at the end of the fortification period;
4. Serum NTBI concentrations at 3 hours after ingesting the first fortificant dose;
5. Faecal calprotectin concentration at the end of the fortification period;
6. *P. falciparum* infection at the end of the fortification period as indicated by whole blood density of asexual parasites or the presence of antigenemia;
7. Adherence to intervention.
8. To compare daily home fortification for 30 days with iron (3mg iron as NaFeEDTA or 12.5 mg iron as encapsulated ferrous fumarate) versus placebo regarding:
   1. The indicators listed under objective 1a-f;
   2. Time to development of anaemia after cessation of iron fortification.
9. To evaluate the accuracy of self-reported adherence with home fortification, using medication events monitoring system as a gold standard.
10. To assess associations between major intestinal parasites and haemoglobin concentration at baseline.
11. To compare intervention effects of iron on intestinal biota.

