**Figure S3: Flow of study participant (incomplete)**

1. **Description of group characteristics at baseline**

For continuous variables, we will visually inspect histograms to assess whether they are normally distributed within intervention groups, with log-transformation of variables with a lognormal distribution. Population characteristics (Table 1) will be reported by intervention group as proportions, means (SD), geometric mean (geometric SD), and median (25th- and 75th percentiles) as appropriate, with corresponding group size. We will not test for group differences for reasons given by Assmann et al. [13].

Table S1: Description of baseline characteristics

| Variable | Type | Units/categories |
| --- | --- | --- |
| Age | Continuous | months |
| Age class | Binary | 12-23 months, 24-36 months |
| Sex | Binary | %males : %females |
| Height-for-age z-score | Continuous | SD |
| Weight-for-height z-score | Continuous | SD |
| Weight-for-age z-score | Continuous | SD |
| Haemoglobin concentration | Continuous | g/L |
| Anaemia status | Ordinal | *Severe to moderate anaemia:* haemoglobin concentration <89g/L; *mild anaemia:* haemoglobin concentration 90-109g/L; *non-anaemic:* haemoglobin concentration ≥110g/L |
| Plasma ferritin concentration | Continuous | μg/L |
| Iron status | Nominal | *Deficient:* plasma ferritin concentration <12 µg/L regardless of presence or absence of infection or inflammation; *replete:* plasma ferritin concentration ≥12 µg/L in the absence of infection or inflammation; *uncertain:* plasma ferritin concentration ≥12 µg/L in the presence of infection or inflammation |
| Plasma soluble transferrin receptor concentration | Continuous | mg/L |
| Plasma C-reactive protein concentration | Continuous | mg/L |
| Plasma *α*_1_-acid glycoprotein concentration | Continuous | mg/L |
| Inflammation | Binary | Plasma concentrations of C -reactive protein (CRP) > 5mg/L and/or α_1_-acid glycoprotein (AGP) > 1g/L |
| Whole blood ZPP concentration | Continuous | μmol/mol haem |
| Erythrocyte ZPP concentration | Continuous | μmol/mol haem |
| *Plasmodium* parasite density (asexual and sexual forms) | Continuous | µL^-1^ |
| *Plasmodium* infection, by rapid dipstick tests | Nominal | No infection; *P. falciparum* (by HRP2 or *P. falciparum*-specific pLDH), other human *Plasmodium* spp. (by pLDH), mixed infection |
| Urinary hepcidin concentration * | Continuous | nmol/mmol creatinine |
| Plasma folate concentration * | Continuous | nmol/L |

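### In the secondary stratified analysis of the primary outcome, the age classes stop at 30 months although the trial population runs to 36 months, so children aged 31-36 months fall in no age stratum

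*SAP*

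**What the plan says.** The section Trial objectives states the population: "In children aged 12-36 months, to compare daily home fortification for 30 days with two iron formulations".

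Table S1, in the section on baseline description, has a binary age-class variable with categories "12-23 months, 24-36 months". These two classes cover the whole range.

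The section Analysis of the primary outcome separates the primary analysis from a list headed as secondary analysis "of the primary outcome will be as follows". The first item on that list is adjustment for selected baseline variables. It names three factors for a stratified analysis: iron status (classes taken from the baseline table), soluble transferrin receptor (split at the median), and "age in classes of children aged 12-23 months and 24-30 months". The stated purpose of the strata is "to allow an assessment of the validity of model assumptions". The accompanying regression models enter "plasma concentrations of ferritin and soluble transferrin receptor and age; as continuous variables".

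**The concern.** The same document defines the age classes in two ways, and the definition attached to the analysis does not cover the trial population. Someone programming the stratified analysis from this section would have no stratum for children aged 31-36 months. They would have to drop those children or depart from the text.

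At stake is the usefulness of one check. The strata are meant to show whether the regression's assumptions hold, and the regression uses every child's age on a continuous scale. If the age strata leave out the oldest children, the top of the age range goes unchecked, the older stratum is estimated less precisely, and the two age strata do not add up to the number analysed. The comparisons of each iron group with placebo are to be done in the same way as the comparison between iron groups, so the same gap would carry over to them.

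**Working it through.** No figure in the plan needs reproducing. The question is which ages the classes cover, and how many children the gap could involve.

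**Inputs**
- Population: 12-36 months (Trial objectives).
- Classes in the stratified analysis: 12-23 and 24-30 months (Analysis of the primary outcome).
- Classes in Table S1: 12-23 and 24-36 months.
- Target size: "The target sample size was 108 participants per group" (Sample size calculations), so 3 × 108 = 324 children.
- Age distribution: not given in the SAP.

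**Coverage, in completed months**
- Classes of the stratified analysis: 31, 32, 33, 34, 35 and 36 fall in neither class.
- Classes of Table S1: no month from 12 to 36 is left out.

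**Size if ages are uniform (assumption).** The answer depends on whether the range includes the whole of the 36th completed month or ends on reaching 36 months.

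| | Includes completed month 36 | Ends on reaching 36 months |
|---|---|---|
| Share of all children dropped | 6/25 = 24% | 5/24 = 21% |
| Share of the 24-36 month class dropped | 6/13 = 46% | 5/12 = 42% |
| Months kept in the older class | 7 of 13 | 7 of 12 |
| Factor on CI width, older stratum | √(13/7) = 1.36 | √(12/7) = 1.31 |

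The factor on CI width assumes the same outcome SD across ages and the same allocation ratio, so that width varies as 1/√n. At 24%, the number dropped is 0.24 × 324 ≈ 78, or about 26 per group.

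**Size without the uniform assumption.** If the share aged 31-36 months lies between 5% and 30% (assumed range):
- 0.05 × 324 ≈ 16 children;
- 0.30 × 324 ≈ 97 children.

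These counts use the target size. The number in the per protocol analysis would be smaller.

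**Is the limit deliberate?** The SAP gives no reason for stopping at 30 months and does not say that older children are to be left out. Where the authors do restrict a subgroup comparison, they say so: for iron status, the subgroup analysis is openly limited to deficient and replete children. The split between 23 and 24 months is the same in both places, and only the upper limit differs. A one-digit slip is the likeliest explanation.

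**The case against.** The strongest reply is that this is a slip which the SAP itself resolves. Table S1 already defines an age-class variable over the full range, and an analyst would most likely use it. That is fair as to intent and explains the low severity. It does not remove the contradiction, because the incomplete classes stand in the section that governs the analysis.

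A reader might infer more than the text supports, in three ways.

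- *That the primary comparison loses children.* It does not. The non-inferiority estimate uses no age strata. The rule that makes the adjusted effect primary when it differs by more than 15% is tied to the comparison of effect estimates with and without adjustment in the regression models. Age is continuous there, so the class limits remove nobody. Age is also not a factor in the separate effect-modification subgroup analysis.
- *That the stratified check fails altogether.* Iron status and transferrin receptor are untouched. Even for age, comparing 12-23 with 24-30 months would still say something about the model, over a narrower range and with less precision.
- *That the older stratum is known to lose about half its children.* That figure follows only from assuming uniform ages. The SAP gives no age distribution, so the size can only be shown as a range.

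**Conclusion.** The inconsistency is certain and needs no assumption: the age classes for the secondary stratified analysis contradict both the stated population and Table S1, and as written they leave children aged 31-36 months unclassified. The effect is confined to the age-stratified part of a secondary analysis, where it narrows the age range checked and lowers precision in the older stratum. How many children are involved is not known from the SAP, and the percentages and counts above hold only under the assumptions stated with them. This is a minor correction on which no main conclusion of the trial depends.

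**What to change.** In the section Analysis of the primary outcome, under adjustment for selected baseline variables, change the older age class from 24-30 to 24-36 months, so that it matches Table S1 and each child falls in exactly one age stratum. The cost is one figure in the SAP. No analysis method, sample size or clinical rule changes.
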